**Methods/design:**

A pilot randomised controlled trial with 18 patients with neurological conditions and mental health disorders will be conducted. Participants attending specialist neurology clinics at a National UK Children’s Hospital will be randomised to receive guided self-help for common mental health disorders or to a 12-week waiting list control. Participants in the treatment group will receive 10 sessions of guided self-help delivered over the telephone. The waiting list control group will receive the intervention after a waiting period of 12 weeks. The primary outcome measure is reduction in symptoms of mental health disorders. Exclusion criteria are limited to those at significant risk of harm to self or others, the presence of primary mental health disorder other than anxiety, depression or disruptive behaviour (e.g. psychosis, eating disorder, obsessive-compulsive disorder) or intellectual disability at a level meaning potential participants would be unable to access the intervention. The study has ethical approval from the Camden and Islington NHS Research Ethics Committee, registration number 14.LO.1353. Results will be disseminated to patients, the wider public, clinicians and researchers through publication in journals and presentation at conferences.

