### Sample size

One of the primary aims of this pilot trial is to estimate the effect size to inform a future full-scale trial. Sample size is therefore estimated from the expected recruitment rate and thus the possible number that can be recruited in one year (the length of the study).

There are 5195 neurology clinic sessions with 2755 patient referrals at GOSH per annum, of which we estimate that two-thirds will fall within the correct age range as patients are seen routinely throughout their childhood (*n* = 1837), and based on clinic data, 15 % will cancel/not attend appointments (*n* = 1561). Of those attending, around 25 % will have an intellectual disability that will mean they are excluded according to criterion 2 in Table 1 [29], leaving *n* = 1170. Assuming 50 % agree to participate (average screening consent rate from Bennett et al., 2015 [24]), we aim to consent 585 participants to the initial screening.

Based on population rates, we conservatively estimate that 10 % of those screened will have a mental health condition warranting intervention (i.e. 59; [35]). Estimating that 66 % will complete the full Development and Well-Being Assessment (DAWBA) [36], around 39 will be potentially eligible for the full intervention. Of these, 40 % (16) may already be receiving input from mental health services [22], leaving 24 young people who are potentially eligible. We estimate that 75 % of these will agree to participate (*n* = 18 children and young people; the mean agreement for intervention rate from Bennett et al., 2015 [24]).

We will only recruit participants whilst there is capacity for intervention. If there is a point at which capacity is almost reached, recruitment and screening will be suspended accordingly. In order to estimate capacity, we will determine a priori how much time each therapist can commit and therefore how many patients they can support per week.

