### Randomisation, blinding and code-breaking

Participants identified by the DAWBA and clinical assessment as experiencing impairing symptoms of mental health disorder and neurological conditions will be randomised to (1) guided self-help for their mental illness over 12 weeks or (2) remaining on the waiting list for guided self-help with no additional intervention over 12 weeks. Stratified by type of mental health disorder (anxiety, depression or disruptive behaviour), participants will be randomised 1:1 to the treatment arms using random blocks. An independent researcher will provide the randomisation codes, hold them and break the code following completion of the trial.

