### Statistical analysis

#### Primary endpoint efficacy analysis

As a pilot, the study is not powered to detect a statistically significant difference between the intervention and waiting list groups. Instead, we will use the results to estimate the effect size of the difference in order to inform a power calculation for a planned full-scale RCT. All analyses will be carried out on an intention-to-treat basis and will be blind to treatment assignment. Treatment groups will be descriptively compared on all baseline measures. No interim analyses are planned, but outcome at the end of treatment will be evaluated prior to data lock for follow-up data. The primary analysis will use the end-of-treatment SDQ assessment to compare the intervention and waiting list control groups. A linear regression adjusting for baseline assessment of the SDQ and other baseline measures for which imbalance is evident will be used to evaluate the intervention effect. Whilst we recognise that the SDQ is not as sensitive at detecting change as other measures such as the RCADS, it is the only measure which is able to detect change across all of the symptoms addressed within the study (anxiety, depression and behavioural difficulties). As diagnosis may be an important moderator of treatment outcome, we will conduct sensitivity analyses by analysing young people with confirmed epilepsy diagnoses (assumed to be the largest subset of participants) separately.

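### The primary regression chooses covariates beyond baseline SDQ by observed imbalance and does not name the stratification factor, so the effect size passed to the full trial depends on which measures look uneven in 18 children

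*Protocol article*

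**What the plan says.** In the Protocol article, the section Primary endpoint efficacy analysis compares the arms on the end-of-treatment SDQ by a linear regression, specified in these terms: "adjusting for baseline assessment of the SDQ and other baseline measures for which imbalance is evident will be used to evaluate the intervention effect". It also says that the arms will be compared descriptively on every baseline measure, that analyses are blind to treatment assignment, and that the resulting effect size will feed the power calculation of a full-scale trial. It gives no list of candidate covariates and no criterion for imbalance. The section Follow-up data applies the same pattern to later outcomes.

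The section Randomisation, blinding and code-breaking says: "Stratified by type of mental health disorder (anxiety, depression or disruptive behaviour), participants will be randomised 1:1 to the treatment arms using random blocks". Disorder type does not appear among the named covariates of the primary model.

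The abstract gives the size: "A pilot randomised controlled trial with 18 patients with neurological conditions and mental health disorders will be conducted". The section Sample size explains its basis: "Sample size is therefore estimated from the expected recruitment rate and thus the possible number that can be recruited in one year".

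**The concern.** Under sound randomisation, any baseline imbalance is chance. A rule that selects covariates on imbalance selects those most collinear with arm, whether or not they predict the SDQ. In 18 children, each one selected uses a degree of freedom and raises the variance of the arm coefficient through collinearity. The pool is not small: RCADS, two PedsQL subscales, IQ, neurological diagnosis, symptom duration and medication are all recorded. Stratified blocks also make disorder type unlikely to look imbalanced, so the rule will tend to leave out the one factor that the design treats as important.

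The effect estimate is one of the pilot's main products, so lack of power is not a defence. As an illustration, required sample size varies with 1/d². If a standardised effect of 0.50 moved by 0.18, the full trial's size would change by a factor of (0.50/0.68)² = 0.54 or (0.50/0.32)² = 2.44.

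**Working it through.** **The plan's own figure.** The recruitment chain in Sample size starts from "There are 5195 neurology clinic sessions with 2755 patient referrals at GOSH per annum" and runs 2755 × 2/3 × 0.85 × 0.75 × 0.50 × 0.10 × 0.66 × 0.60 × 0.75 = 17.4 without intermediate rounding, against 18 stated. It reproduces within rounding. At 1:1 this gives about 9 per arm.

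**Chance imbalance at 9 v 9.**
- The standard error of a standardised difference is √(2/9) = 0.471.
- 0.5/0.471 = 1.06, so P(|difference| > 0.5) = 0.29 (normal) or 0.30 (t, 16 df). For a cut-off of 0.25 it is 0.60.
- With 6 independent candidates and a cut-off of 0.5, about 6 × 0.30 = 1.8 are picked, and at least one in 89% of trials. With 8, about 2.4 are picked, and at least one in 95%.

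**Benchmark.** With baseline correlation 0.5 (assumed), the half-width adjusting for baseline SDQ alone is about t(15) × √[(1 − 0.25) × 2/9] = 2.131 × 0.408 = 0.87 SD. Simulation gives 0.88.

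**Simulated interval widths.** Set-up: 18 children, three strata of 6, 3 v 3 in each, ordinary least squares, two-sided 95% t-interval, 4,000 or 6,000 trials per scenario. The document does not give the baseline correlation, stratum sizes, number of candidates, cut-off, or the share of SDQ variance explained by disorder type or by the candidates. All are assumptions. Half-widths are in SD units, and percentages come from unrounded values.

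| Candidates | Cut-off | Variance explained by candidates | By stratum | SDQ + stratum | Imbalance rule | Difference |
|---|---|---|---|---|---|---|
| 4 | 0.5 | 36% | 0% | 0.90 | 0.92 | +2% (mean) |
| 4 | 1.0 | 0% | 0% | 0.90 | 0.92 | +3% (mean) |
| 4 | 0.8 | 0% | 0% | 0.90 | 0.94 | +5% (mean) |
| 6 | 0.5 | 36% | 0% | 0.89 | 0.95 | +7% (median) |
| 4 | 0.8 | 0% | 10% | 0.83 | 0.95 | +14% (mean) |
| 6 | 0.5 | 0% | 0% | 0.89 | 1.02 | +15% (median) |
| 6 | 0.5 | 0% | 9% | 0.84 | 1.03 | +23% (median) |
| 8 | 0.5 | 0% | 10% | 0.84 | 1.12 | +34% (mean) |
| 6 | 0.5 | 0% | 25% | 0.73 | 1.04 | +44% (median) |

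**Movement of the point estimate** from the SDQ-only model, mean absolute shift with non-prognostic candidates: about 0.04 SD (4 candidates, cut-off 1.0), 0.14 (4, cut-off 0.5), 0.18 (6, cut-off 0.5; 90th percentile 0.43) and 0.23 (8, cut-off 0.5).

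**Bias and residual variance.** Average bias was below 0.02 SD. Mean residual variance was 0.761 under the rule v 0.760 with baseline SDQ alone when candidates are noise, and 0.649 v 0.745 when they are prognostic.

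**The stratum alone** (baseline SDQ only v baseline SDQ + stratum, half-width):
- disorder type explains nothing: 0.88 v 0.89;
- about 10% of variance: 0.89 v 0.84;
- 25%: 0.90 v 0.73.

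At 25% the estimate itself varies about equally in both models (SD 0.352 v 0.348). Omission mainly makes the reported interval too wide: coverage was about 0.98 in a run with varying stratum sizes.

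**The case against.** The best defence is that the candidates are not noise. RCADS and PedsQL emotional functioning measure symptoms close to the SDQ, and a careful analyst may call only large gaps imbalanced. This stands in part. Under such assumptions the interval penalty falls to a few per cent. With four candidates explaining 36% of variance, the true spread of the estimate even falls (SD 0.39 v 0.43). That gain comes from the covariates being prognostic, not from their being imbalanced, and naming them in advance would secure it without the data-dependence.

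Blind analysis is a second safeguard. It limits steering towards a favoured arm. It does not remove the dependence on the data, because imbalance between two coded groups remains visible.

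Third, with 18 children the estimate is imprecise under any model: a half-width of about 0.84 to 0.90 SD in most scenarios with a fixed model. This is true, and it keeps the point in proportion, but the change is nearly free.

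A reader might infer more than the document supports:
- that the rule biases the effect (it does not, on average);
- that it inflates the variance carried to the full trial (the residual variance is unchanged, or falls; what usually widens is the interval for the arm effect);
- that omitting the stratum must widen the interval (only if disorder type predicts SDQ, for which no figure is given);
- that one figure, such as 1.12 v 0.84 SD, measures the harm (it is one unfavourable set of assumptions).

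Nor can this be passed over as detail left to an analysis plan. The article states a covariate rule, and a plan that followed it would inherit the weakness.

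**Conclusion.** The concern holds in limited form. The stated model lets chance imbalance in about 9 v 9 children decide the covariates, and it does not name the factor used to stratify. The consequences are an effect estimate that depends on what looks uneven (mean shift about 0.04 to 0.23 SD) and, usually, a 95% interval wider than that from baseline SDQ + stratum, by about 2% to 44%. Both ranges depend on the number of candidates, the meaning given to imbalance, and whether the candidates and disorder type predict SDQ. The existence of the data-dependence is certain from the text; its size is not. There is no average bias and no inflation of residual variance. The change is worth making because it is cheap and the estimate feeds a power calculation, but it is secondary to the imprecision of a trial of 18.

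**What to change.** State the primary model as SDQ at the primary endpoint on arm, baseline SDQ and disorder-type stratum as randomised, with a rule for collapsing sparse strata set before unblinding. Delete the clause that adds other baseline measures on the strength of imbalance, and keep the baseline comparison descriptive. Put any further adjustment in a labelled sensitivity analysis, with covariates named before unblinding for their expected prognostic value. Carry the same model to the follow-up outcomes.

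The cost is a change of a few sentences, with no new data, visits or patients. The strata use two degrees of freedom. If disorder type explains nothing, the half-width rises by about 1.5% (0.88 to 0.89 SD). Some precision may also be lost if a dropped covariate such as RCADS is strongly prognostic. If the sponsor expects that, it can name the covariate in the primary model in advance.

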#### Follow-up data

Outcome analyses will follow the pattern of those of the primary endpoint. Outcomes will be reported in accordance with the Consolidated Standards of Reporting Trials (CONSORT) statement.

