## Methods/design

### Study design

The study is a pilot RCT conducted at Great Ormond Street Hospital (GOSH), UK. Eligible children attending a neurology clinic and who have impairing symptoms of common mental health disorders (anxiety, depression and/or disruptive behaviour) will be randomly allocated to either (1) receive guided self-help for their mental health disorder over 12 weeks or (2) remain on a waiting list for 12 weeks with no additional intervention. Children randomised to the waiting list condition will be offered the guided self-help intervention at the end of 12 weeks. All participants will complete follow-up assessments at 4 and 12 weeks post-intervention (Fig. 1). Methods are in accordance with the Standard Protocol Items: Recommendations for Interventional Trials (SPIRIT) statement (Additional file 1).

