### Ethical and safety considerations

It is possible that the questionnaires, assessment and intervention may cause participants and/or carers to become distressed. The research team is made up of a number of clinically trained researchers, who will be well-placed to manage this distress should it arise and to signpost to sources of support (such as local mental health services) if necessary. Some participants will be randomised to remaining on the waiting list. However, all children will eventually receive the guided self-help intervention. We are not depriving any children of an intervention that they would otherwise have received.

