## Trial status

Recruitment began in January 2015 and recruitment to the study is due to end in January 2016 with all participants completing follow-up by August 2016.

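### The follow-up analysis inherits a between-arm comparison that no longer has an untreated control, so its arm coefficient estimates neither the intervention effect nor its durability; the stated completion date also does not fit the waiting-list path

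*Protocol article*

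**What the plan says.** All references are to the protocol article.

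- **Follow-up data** gives one rule: "Outcome analyses will follow the pattern of those of the primary endpoint".
- **Primary endpoint efficacy analysis** defines that pattern: "The primary analysis will use the end-of-treatment SDQ assessment to compare the intervention and waiting list control groups". The model is given as "A linear regression adjusting for baseline assessment of the SDQ and other baseline measures for which imbalance is evident will be used", with the stated purpose of evaluating the intervention effect. The same section places every analysis on an intention-to-treat basis, that is, by randomised arm.
- **Study design** sets the crossover and the visits: "Children randomised to the waiting list condition will be offered the guided self-help intervention at the end of 12 weeks" and "All participants will complete follow-up assessments at 4 and 12 weeks post-intervention". **Follow-up assessments** anchors these visits to completion of the intervention, not to randomisation.
- **Ethical and safety considerations** adds that "all children will eventually receive the guided self-help intervention".
- **Trial status** gives the timetable: "recruitment to the study is due to end in January 2016 with all participants completing follow-up by August 2016".

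No section gives a different target for the follow-up data, such as maintenance of gains or pooled within-child change.

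**The concern.** A regression on arm estimates a treatment effect only while one arm is untreated. In this design that ends at week 12. Carrying the same model forward produces a number that looks like the primary result at a later time but answers a different question.

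A reader who sees a difference at week 12, then differences near zero from the same model at follow-up, could naturally conclude that the benefit faded. The pilot exists to inform a powered trial, so an uninterpretable follow-up coefficient could feed into decisions about that trial's follow-up.

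Separately, the longest path through the trial appears too long for the stated completion date, and only the waiting-list arm is affected.

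**Working it through.** **1. Visit times from randomisation**

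Inputs: a 12-week wait (Study design), a 12-week intervention (Guided self-help arm), and follow-up at 4 and 12 weeks after completion (Follow-up assessments). The sums assume exact intervals and no gap before treatment starts.

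| | Intervention arm | Waiting-list arm |
|---|---|---|
| Treatment ends | 12 | 12 + 12 = 24 |
| First follow-up | 12 + 4 = 16 | 24 + 4 = 28 |
| Second follow-up | 12 + 12 = 24 | 24 + 12 = 36 |

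Matching on time since randomisation does not restore a control. At week 16 the waiting-list arm is 4 weeks into treatment with no outcome visit listed under Assessments. At week 24 it is at its own end of treatment.

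**2. What the arm coefficient estimates**

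Let n(t) be the mean SDQ change by week t without treatment, and e(k) the treatment effect k weeks after completion, assumed equal in both arms. Given equal baselines, the differences (intervention minus waiting list) are:

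- Week 12: [n(12) + e(0)] − n(12) = e(0). This is the intervention effect.
- Follow-up visit k: [n(12 + k) + e(k)] − [n(24 + k) + e(k)] = n(12 + k) − n(24 + k).

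At follow-up e(k) cancels. What remains is 12 weeks of untreated drift with the sign reversed, and it is zero if there is no drift. The result is the same whether e(k) is large, small, maintained or lost.

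If only a fraction p of the waiting-list arm takes up the offer, against full uptake in the intervention arm, the coefficient also contains (1 − p)·e(k). That is a diluted effect whose size depends on uptake.

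**3. The timetable**

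The stated figure is all follow-up complete by August 2016, with recruitment ending in January 2016. Adding each path to randomisation dates of 1 and 31 January 2016 gives:

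- Intervention arm, 24 weeks: 17 June to 17 July 2016. This fits.
- Waiting-list arm, first follow-up, 28 weeks: 15 July to 14 August 2016. This fits a 31 August limit.
- Waiting-list arm, second follow-up, 36 weeks: 9 September to 9 October 2016. This does not fit; it is 9 to 39 days past 31 August.

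Working backwards, 31 August 2016 less 36 weeks is 23 December 2015, and 1 August 2016 less 36 weeks is 23 November 2015.

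The number affected assumes uniform accrual and 9 waiting-list children (18 randomised 1:1). The exact start and end days within each January are not given, so three windows are shown.

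| Recruitment window | Late for 31 August | Late for 1 August |
|---|---|---|
| 1 Jan 2015 to 1 Jan 2016 (365 days) | 9 × 9/365 = 0.2 | 9 × 39/365 = 1.0 |
| 1 Jan 2015 to 31 Jan 2016 (395 days) | 9 × 39/395 = 0.9 | 9 × 69/395 = 1.6 |
| 31 Jan 2015 to 31 Jan 2016 (365 days) | 9 × 39/365 = 1.0 | 9 × 69/365 = 1.7 |

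**The case against.** - **The sentence does not itself say between arms.** It could mean only the same model family, intention-to-treat and blinding, and an unseen analysis plan may say more. That reading is possible but less natural: the pattern adopted is defined as a comparison of the two arms, and no other follow-up target is given. The gap lies in what the article states, not in detail it leaves out.
- **Misreading is not written into the plan.** A reader might infer that a null follow-up difference would be reported as an effect not maintained. The protocol says no such thing and states no durability hypothesis. What stands is a risk of misinterpretation.
- **Not every child will necessarily be treated.** Study design and the Waiting list control arm section speak of an offer; only the ethics section says "all children will eventually receive the guided self-help intervention". Some may decline. That leaves the diluted mixture shown above, not an untreated control.
- **The date is a forecast.** A reader might infer that the timetable cuts off the last waiting-list visit. Trial status sets no data cut-off, and the visit could simply take place in September or October. The inconsistency stands; loss of data does not follow from it.
- **Follow-up is secondary in an 18-child pilot.** This is right, and it limits the severity. The effect size for the future trial comes from the end-of-treatment comparison.

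**Conclusion.** The point holds as a fault in the stated follow-up analysis that should be fixed but does not threaten the trial's main output. Under the stated rule, the arm coefficient at both follow-up visits compares immediate with delayed treatment, with assessments 12 weeks apart in time since randomisation. Its expected value is near zero if both arms respond alike and untreated symptoms do not drift, so it is uninformative about effect or durability. The week-12 comparison is unaffected, provided that the waiting-list arm contributes its end-of-wait assessment.

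The timetable is a minor, separate inconsistency: at most about one waiting-list child for a 31 August limit and fewer than two for 1 August. This rests on uniform accrual and exact intervals. Any delay between randomisation and the start of treatment, or at the end of the wait, would lengthen the path.

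**What to change.** **Analysis.** State that the randomised comparison is made only at 12 weeks, end of treatment against end of waiting list. Report the follow-up visits as uncontrolled within-child change, by arm and pooled, with 95% confidence intervals, and label this as not a treatment comparison. Measure change from end of treatment, which describes maintenance. Add change from the start of treatment only if the SDQ is recorded at the end of the waiting period. The section on the baseline and post-waiting-list assessment names only the anxiety and depression scale (RCADS) and the quality-of-life inventory (PedsQL). The primary comparison needs that SDQ as well, so it is worth stating explicitly.

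**Timetable.** Restate completion as mid-October 2016, or give the last-randomisation date that the stated end implies: 23 December 2015 for 31 August, or 23 November 2015 for 1 August.

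**Cost.** A few sentences and one date. The trial gives up any between-arm claim about durability, which the design cannot support. Change measured from the screening SDQ would include regression to the mean and must be described that way. Restating the completion date loses no children. An earlier last-randomisation date would apply to both arms and, under uniform accrual, forgo about 0.4 to 1.9 of 18 children for 31 August (18 × 9/365 to 18 × 39/365), or 1.9 to 3.4 for 1 August (18 × 39/365 to 18 × 69/365).
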